### Additional consent provisions for collection and use of participant data and biological specimens {26b}

Not applicable. No biological specimens will be obtained.

### Interventions

#### Explanation for the choice of comparators {6b}

Patients in the CG also have an indication for knee or hip replacement and receive the current state-of-the-art, gold standard therapeutic intervention (TJA). The comparator group differs from the IG in the fact that patients cannot use the functions of the “alley” application. Since alley is an accompanying adjuvant eHealth intervention, this type of CG is well-suited to directly compare the effects of the app solely. Nevertheless, the (non-functional) application must be installed on a smartphone or an internet-enabled mobile device as it is used for the questionnaire survey and data entry.

#### Intervention description {11a}

The adjuvant use of the “alley” eHealth application in addition to TJA is defined as IG. The application is hosted by the VBMC ValueBasedManagedCare GmbH and is offered for Android and Apple mobile devices. The application is intended to prepare and accompany hip or knee arthroplasty. The application contains educational content, which is displayed on the patient’s smart device according to their actual individual needs within the healthcare system. The program and its contents were systematically developed by a multi-professional team consisting of medical physicians, psychologists, health scientists, economists, and computer scientists. The development was realized in a multi-stage process with the involvement of all project partners and external consultants. Development was based on existing guidelines and evidence-based materials for patient information. Didactically, text-based information modules were elaborated to guide patients through the health care system before and after surgery. The app provides comprehensive information to empower the patients. Patients receive push notifications on their mobile phones at regular intervals before and after surgery. The content of patient education is structured into three dimensions: (1) informative (information about daily life with osteoarthritis, origin of pain, treatment options, surgical procedures, daily life with joint replacement), (2) organizational (information about important contact persons after surgery, medical rehabilitation proposal, medical and non-medical remedies and aids), and (3) emotional/empowerment (information about rehabilitation targets, relationship between mood and pain, new habits, managing daily challenges). In summary, patients receive information about the disease, its treatment and aftercare as well as strategies for actively coping with the disease and its implications. These include cognitive and behavioral strategies for emotional relief, well-being, and social support. The app further provides information about which medical documents should be brought to the attending physician and which topics may be relevant to ask during a doctor’s consultation.

In the app, patients have the possibility to evaluate their condition and functional level by means of standardized medically validated questionnaires. Data on pain and functioning can continuously be entered by patients as personal monitoring.

In the IG, these patient’s data can be displayed on the physician’s web-based dashboard in the hospital to provide in-depth patient-reported information during operational reconnaissance. In line with the general purpose, the collected information is to be used in a supportive and accompanying manner by the patient and service providers involved to improve quality and optimize diagnostics and therapy. The aim of the application is to guide patients with osteoarthritis of the hip a knee through the health care system, to provide support for these patients, and to provide the attending physician with continuous information about the patient’s health. The patient reported outcome questionnaires implemented in this study are not only used as part of it but represent an integral part of the application enabling patients to report their actual condition to their treating physician at any time.-The app intervention therefore promotes individualized medicine. In the context of the study, the use of the web-based dashboard by physicians is optional.

#### Criteria for discontinuing or modifying allocated interventions {11b}

A discontinuing or modifying allocated intervention during the study period is not foreseen. The programming code of the application cannot be changed or adapted during the study. External conditions, e.g., arthroplasty joint revisions, have no influence on the use of the app. On the contrary, postoperative complications should be recorded descriptively with the application at follow-up.

### Strategies to improve adherence to interventions {11c}

Patients are reminded via push notification when new content is available to read. The notifications remain in the alley application until the corresponding information article has been read. In addition, each patient receives 150 EUR after the questionnaire has been completed 3 months after surgery.

### Relevant concomitant care permitted or prohibited during the trial {11d}

The study is designed within the scope of health services research to evaluate alley in the real environment. Accordingly, all additional interventions, by the patient, e.g., physical therapy, additional pain medication are permitted and are surveyed.

### Provisions for post-trial care {30}

Patients can continue to use the app for self-monitoring after the trial. The patients who were initially in the CG get access to the educational materials in the alley application after 12 months, when the trial is completed.

### Outcomes {12}

Standardized and self-constructed questionnaires are applied to operationalize the target criteria. After registration with alley, all patients undergo an onboarding process, in which patients complete the medical questionnaires. In total, patients are surveyed at six measurement time points: Baseline before the surgery (*t*_0_) and 10 days after surgery (*t*_1_) as well as 1 (*t*_2_), 3 (*t*_3_), 6 (*t*_4_), and 12 months (*t*_5_) after TJA.

The primary outcome is change from baseline in functional status measured by the Hip Osteoarthritis Outcome Score (HOOS) or Knee injury and Osteoarthritis Outcome Score (KOOS) 3 months after TJA. The statistical analysis will be carried out separately for the two medical indications. Further secondary endpoints of the study are depression, anxiety, physiological, mental, and social health, pain, risk of falling, dispositional optimism and pessimism, patients’ expectation, post-operative complications, satisfaction with treatment, perceived knowledge of the patient about the disease, and health literacy. The secondary endpoints will also be analyzed separately for patients with hip and knee complaints. An overview of the instruments and measurement times is given in Table 2.

**Table 2 Tab2:** Target criteria, assessment instruments, and measurement time points

Target criteria	Assessment instruments	Measurement time points					
		***t***_***0***_	***t***_***1***_	***t***_***2***_	***t***_***3***_	***t***_***4***_	***t***_***5***_
**Primary outcome**							
Joint functioning	Patients with hip replacement: Hip Osteoarthritis Outcome Score (HOOS [22];)	X	X	X	X	X	X
	Patients with knee replacement: Knee injury and Osteoarthritis Outcome Score (KOOS [23];)	X	X	X	X	X	X
**Secondary outcomes**							
Pain	Visual analog scale (VAS)	X	X	X	X	X	X
Depression and anxiety	Depression, anxiety and stress scale (DASS [24];)	X	X	X	X	X	X
Physiological, mental, and social health	Patient-Reported Outcomes Measurement Information System (PROMIS®-29 [25];)	X	X	X	X	X	X
Patients’ expectations	Credibility/expectancy questionnaire (adapted from [26])	X	X	X	X	X	X
Patient satisfaction	Patients’ Experience Questionnaire (PEQ [27];)			X	X		
Dispositional optimism and pessimism	Life-Orientation-Test (LOT-R [28];)	X			X	X	X
Risk of falling	Self-constructed questionnaire	X			X	X	X
Post-operative complications	Self-constructed questionnaire		X	X	X	X	X
Knowledge about the disease (patients’ health literacy)	Self-constructed questionnaire	X	X				
Knowledge about postoperative behavior (patients’ health literacy)	Self-constructed questionnaire	X	X				
Perceived knowledge of the patient about the disease (Physician questionnaire)	Self-constructed questionnaire	X					
Sociodemographic variables	ICHOM standard set for hip- and knee osteoarthritis (International Consortium for Health Outcomes Measurement)	X					

### Participant timeline {13}

An overview over the participant timeline is provided in the flowchart in Fig. 1 and supplemented with the questionnaires to be completed in Table 2. The patients complete various questionnaires at six measurement points. This results in a study time expenditure of approx. 180 min for the patients.

**Fig. 1 Fig1:**
[figure not shown]
Trial design

### Sample size {14}

The sample size was calculated considering the expected effect size, power, measurement time point, and design effect and was performed with the open access program G*POWER [29]. The statistical analysis and corresponding sample size calculation are conducted separately for hip and knee patients.

#### Sample size calculation for patients with osteoarthritis of the hip

The sample size calculation for patients with osteoarthritis of the hip is based on an average change score of 9 points with a standard deviation of ± 15 points in the total score of HOOS observed in other intervention studies after three months [30, 31]. Based on this data available, an effect of 0.6 can be assumed. With a standard α-risk of 0.05 and a statistical power of 0.8 (1 – β), a sample size of *n* = 61 patients in each group is required to obtain significant differences in Student’s *t*-test for independent variables. This number of cases will be enlarged to consider any potential data missing. Due to observed dropout rates of up to 20% [32], exclusion of patients due to errors in data entry (4%) [33], an approximate across-the-board increase due to the risk of complications due to corona the number of patients to be included is increased to achieve the required sample size at the time of measurement 3 months post-surgery. Therefore, *n* = 100 participants and *n* = 100 controls were supposed to be recruited for the THA evaluation group.

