#### Sample size calculation for patients with osteoarthritis of the knee

The required sample size for patients with osteoarthritis of the knee is also calculated using data from the literature [30, 34, 35]. Similar to the results on the hip, we derived an average change score of 9 points with a standard deviation of ± 15 points in the total score of the KOOS yielding to an expected effect size of 0.6. With an α-risk of 0.05 and a statistical power of 0.8 (1 – β), a sample size of *n* = 61 patients in each group is required to obtain significant differences in Student’s *t*-test for independent variables. The number of required cases is further expanded to consider any missing. I summary, *n* = 100 patients and *n* = 100 controls were supposed to be recruited for the TKA evaluation group.

Therefore, the total number of patients to be included is *n* = 400.

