### Statistical methods

#### Statistical methods for primary and secondary outcomes {20a}

A two-arm evaluation will be performed. In one arm, all patients of the “hip intervention group” and their CG are analyzed. In the other study arm, the evaluation of the “knee intervention group” and their corresponding CG is carried out. A combination of the data from the two study arms is not intended. The statistical analysis is performed separately for patients with TKA and THA by means of mean, median, standard deviation, and quantiles to initially depict the patient collectives and the primary and secondary endpoints descriptively. The Kolmogorov-Smirnov test as well as histograms and QQ-plots are applied to evaluate normal distribution of all continuous variables. Differences at baseline between IG and CG are assessed with Student’s *t*-test for independent variables in case of normally distributed data or with the Mann-Whitney *U* test in case of non-normal distribution. Categorical variables are examined by *χ*^2^ or Fisher’s exact test. If differences are observed, data risk adjustment with logistic regression is applied.

To evaluate outcome differences between the groups, delta values (change scores) are calculated in each group between the adjacent measurement time points (ti-tj, j > i) for each variable. To address our main superiority hypothesis, delta values from baseline to 3 months post-surgery of the IG and CG are statistically examined using Student’s *t*-test for independent variables. Additionally, Cohen’s *d* effect size and its 95% confidence interval will be calculated. Cohen’s *d* is a measure of the effect size for mean difference between two samples regarding interval-scaled variables. Values of *d* = 0.20 represent small, *d* = 0.50 medium, and values from *d* = 0.80 large effect [36]. In the case of non-normally distributed data, the Mann-Whitney *U* test is applied. To investigate differences at the follow-up measurement time points, further *t*-tests were performed. Because of multiple testing, an alpha error correction according to Bonferroni will be applied.

Significant differences between the several measurement times *t*_0_ to *t*_5_ are evaluated with analyses of variance with repeated measures and paired Student’s *t*-test for normally distributed data. The Friedman test and the Wilcoxon test are used in the case of non-normally distributed data.

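### The stated inputs (d = 0.6, alpha 0.05, power 0.8) give 45 patients per group, not the 61 stated for both hip and knee

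*Protocol article*

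**What the plan says.** The Sample size section {14} of the protocol article says that the calculation was done in G*Power, separately for hip and knee, and took account of effect size, power, measurement time point and a design effect. No value for the design effect appears anywhere.

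The hip paragraph starts from "an average change score of 9 points with a standard deviation of ± 15 points in the total score of HOOS" and concludes that "an effect of 0.6 can be assumed". It continues "With a standard α-risk of 0.05 and a statistical power of 0.8", and from this "a sample size of *n* = 61 patients in each group is required" for Student's t-test on independent groups. Only then is the number raised, for dropout of up to 20%, data-entry exclusions of 4% and a general allowance for the pandemic, to 100 per arm.

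The knee paragraph repeats the 9 points, the SD of 15 and the effect size of 0.6, then "With an α-risk of 0.05 and a statistical power of 0.8", and reaches the same 61 and the same 100 per arm.

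Neither paragraph says whether alpha is one-sided or two-sided. The statistical methods {20a} do not say either. They name the independent-groups test for the primary comparison but no direction; the sentence begins "To address our main superiority hypothesis, delta values from baseline to 3 months post-surgery of the IG and CG are statistically examined using Student’s".

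**The concern.** Each paragraph lists everything that a two-group t-test calculation needs except the sidedness, and attributes 61 directly to that list. A reader who repeats the calculation does not get 61 under either sidedness. So at least one reported input is not the one used, or a further input was used and left out.

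At stake is how the results will be read. Hip and knee are analysed as two separate comparisons, and a null result in either will be judged against the power statement. As printed, nobody can tell whether 61 evaluable patients per arm stand for 80%, 91% or 95% power, at which sidedness, or with what allowance for clustering.

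A smaller ambiguity sits in the same sentence. The t-test needs a between-arm difference in change. The hip calculation "is based on an average change score of 9 points with a standard deviation of" 15, and the statistical methods use the similar term for something computed within each arm: "delta values (change scores) are calculated in each group". The sample size text does not say which of the two the 9 points is.

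**Working it through.** **Inputs** (same in the hip and knee paragraphs): difference 9, SD 15, alpha 0.05, power 0.80, independent-groups t-test. Allocation is 1:1 (Sequence generation {16a}). Sidedness is not stated, so both are tried.

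**Effect size.** d = 9/15 = 0.6. This reproduces the article's figure.

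**Normal approximation.** n per group = 2(z_alpha + z_beta)²/d².
- Two-sided: 2 × (1.960 + 0.842)²/0.36 = 43.6, so 44.
- One-sided: 2 × (1.645 + 0.842)²/0.36 = 34.3, so 35.

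**Exact noncentral t** (the method that G*Power uses): df = 2n − 2, noncentrality = d√(n/2).
- Two-sided, power 0.80: n = 44.6, so 45 (achieved power 0.804).
- One-sided, power 0.80: n = 35.04, so 36.

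The stated 61 is not reproduced. It exceeds 45 by 16 patients per group (16/45 = 36%).

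**Power that 61 per group gives at d = 0.6, no design effect.** Noncentrality = 0.6 × √30.5 = 3.314, df = 120.
- Two-sided: 0.908.
- One-sided: 0.951.

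**Can missing data explain it?** 45/0.80 = 56.3 (57); 45/(0.80 × 0.96) = 58.6 (59); 45/0.76 = 59.2 (60). None is 61, and the hip paragraph makes this allowance after the 61, so it would be counted twice.

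**Changes to the inputs that do give about 61:**

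| Change | n per group |
|---|---|
| One-sided alpha 0.05, power 0.95 | 61 (60.8) |
| Two-sided alpha 0.05, power 0.90 | 60 (59.4) |
| Two-sided alpha 0.025, power 0.85 | 61 |
| Two-sided alpha 0.0167, power 0.80 | 60 |
| d about 0.51, two-sided alpha 0.05, power 0.80 | 61 |
| 45 × design effect of about 1.35 | 60.75, so 61 |

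Several different changes fit, so the arithmetic cannot show which one was made.

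**Is planned enrolment too small?** With no design effect, two-sided power at d = 0.6 is 0.957 for 76 per arm (100 less 24%), 0.965 for 80 (100 less 20%) and 0.988 for 100.

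**Detectable difference** (80% power, two-sided alpha 0.05, SD 15, no design effect):
- 61 per arm: d = 0.511; 0.511 × 15 = 7.7 points.
- 76 per arm: d = 0.457; 0.457 × 15 = 6.9 points.

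**The case against.** The strongest defence is the design effect. The Sample size section says that one was considered, the trial has eight sites, and a multiplier of about 1.35 would take 45 to 61 at exactly the stated power. A reader might infer from the arithmetic that the stated power is wrong. The document does not support that, because the power may be right and the multiplier merely unreported. This part of the defence stands. It does not rescue the text: no value is given, both paragraphs attribute 61 to alpha, power and the t-test alone, and the planned primary analysis is an ordinary t-test with no term for site.

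A second defence is that the error does no harm, since 61 is more than 45 and 100 per arm are recruited. On the stated d and without a design effect, this is correct, and it limits how serious the point is.

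A reader might also infer that the 9 points is a within-arm change, so that true power is far below 80%. The document does not support this either. The figure comes from cited studies that are not shown, and it is used directly as the effect for an independent-groups test, which fits a between-arm difference. The statistical methods describe how this trial forms its change scores; they do not define the term in the sample size text. Any power quoted for a smaller difference would rest on a value that the article does not give. What remains is a fair request for one clarifying phrase.

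**Conclusion.** The point holds as an error of arithmetic or reporting, in both indications: d = 0.6, alpha 0.05 and power 0.8 give 45 per group two-sided or 36 one-sided, not 61. If no design effect was applied, 61 per group has about 91% power two-sided or 95% one-sided. If one was applied, it was about 1.35 (taking the test as two-sided) and should have been printed. Which input is misreported cannot be decided from the document.

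These figures assume equal groups, a common SD of 15 for the change score, and the 9 points read as a between-arm difference. On the stated effect the discrepancy is conservative. Neither the primary test nor the enrolment of 100 per arm needs to change, and the document gives no ground for calling the trial underpowered.

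**What to change.** Correct both paragraphs so that the inputs and n agree.

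1. State whether alpha 0.05 is one-sided or two-sided.
2. Then choose the alternative that matches what was done:
   - (a) No design effect was applied: delete the term, and state 45 per group for 80% power or 61 per group for about 91% (two-sided).
   - (b) A design effect was applied: give its value and show that 45 × design effect = 61. In this case the 91% figure must not be printed.
3. In the same sentence, state that 9 points is the assumed between-arm difference in change. If the cited sources give a within-arm change, replace it with the detectable difference: about 7.7 points at 61 per arm or about 6.9 points at 76 per arm (two-sided, SD 15, 80% power, no design effect).

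If the test is one-sided, the figures in steps 2 and 3 have to be restated to match (36 per group for 80% power; about 95% at 61).

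The cost is rewording two paragraphs, after a look at the saved G*Power entries and the cited sources. Enrolment and the primary test stay as they are.

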#### Sample size calculation for patients with osteoarthritis of the knee

The required sample size for patients with osteoarthritis of the knee is also calculated using data from the literature [30, 34, 35]. Similar to the results on the hip, we derived an average change score of 9 points with a standard deviation of ± 15 points in the total score of the KOOS yielding to an expected effect size of 0.6. With an α-risk of 0.05 and a statistical power of 0.8 (1 – β), a sample size of *n* = 61 patients in each group is required to obtain significant differences in Student’s *t*-test for independent variables. The number of required cases is further expanded to consider any missing. I summary, *n* = 100 patients and *n* = 100 controls were supposed to be recruited for the TKA evaluation group.

Therefore, the total number of patients to be included is *n* = 400.

### Recruitment {15}

Recruitment is performed by medical consultants in each of the eight study locations. Immediately after surgery indication for total hip/knee arthroplasty (THA/TKA), patients will be informed about the study and receive further information material. The patients are addressed directly by the attending physician, which increases compliance to study participation. Each study site recruits both patients with knee or hip problems and allocate these patients to the corresponding group based on the randomization sequence.

### Assignment of interventions: allocation

#### Sequence generation {16a}

A 1:1 randomization has been conducted, assigning patients to either CG or IG for THA or TKA, respectively. For this purpose, two randomization lists have been created using Excel random number generator, creating separate lists for THA and TKA. These lists contained a predefined identification code for each indication, which was randomly assigned to the IG or CG. If patients agreed to participate, they were assigned to this list and thus received a unique identification code. This personal code serves as login for the “alley” application. As the randomization list was a shared online document for all study sites, simultaneous double submissions had to be avoided. For this reason, block randomization has been used for blocks of 50 patients. This means that each of the eight study sites is allocated to a fixed slot of 50 patients on the randomization list. During patient recruitment, these slots are successively filled. If more than 50 patients are to be recruited, new slots can be released at the end of the list. The randomized allocation of patients to either IG or CG allows minimizing the inclusion of patients with strong affinity for using digital applications in the IG. Randomization will ensure an equal distribution of patients.

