### Trial design {8}

The trial is planned as a prospective, randomized, controlled, non-blinded multi-center study to compare “alley” with standard treatment with scope of a superiority study design in two independent indications. Two hundred patients scheduled for THA and 200 patients scheduled for TKA will be independently randomly assigned to the IG or CG. Assessments will be performed at baseline before TJA (*t*_0_), 10 days after TJA (*t*_1_), 1 months after TJA (*t*_2_), 3 months after TJA (*t*_3_), 6 months after TJA (*t*_4_), and 12 months after TJA (*t*_5_).

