## Methods: participants, interventions, and outcomes

### Study setting {9}

The study will be conducted in eight clinical sites in Germany. A total of two academic hospitals and six community clinics participate in the study. The full list of these clinics can be obtained via German Clinical Trials Register (https://www.drks.de/) under the registration code DRKS00025608.

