## Strengths and limitations

The present study will have clear strengths and weaknesses. Methodologically, the study is designed as a prospective, randomized, controlled, multi-center trial with clear inclusion and exclusion criteria. Although the basic conditions of the patients are similar in all clinics, it cannot be excluded that clinic-internal processes or procedures influence the change in outcome (e.g., different surgical accesses, special pain management within a clinic, etc.). Since the study examined the effectiveness under everyday conditions, it could not be controlled whether patients in the IG read the patient-educational information provided by the “alley ortho companion” app or whether patients in the CG did consume additional information from the Internet or brochures in preparation for TJA. However, this type of study design increases the external validity, which improves the generalizability of the study results. Concurrently, it should be noted that there are certain limitations regarding the transferability of the results to the general target group of the application. The external validity could be distorted by the incentive of 150 EUR per patient. We cannot exclude the possibility that the patients have engaged with the app particularly intensively for this reason. Nevertheless, we believe that differences in the HOOS and KOOS score between the IG and CG can still be directly attributed to the intervention due to the randomized controlled trial design. Another limitation is that the use of a digital application requires the ownership of a mobile device, the ability to handle the device, and the ability to handle the app itself. Due to the advanced age of the patients with osteoarthritis, some individuals could be systematically excluded from the effects of the intervention. For these patients, the most important core information from the alley application could be provided to as written handout or brochure. To systematically examine this potential third study arm, the sample size would have had to be highly increased, which was not possible for logistical and economic reasons in the current design.

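### Site slots of 50, with about 25 patients expected per site and indication, do not ensure balanced arms, and the primary t-test leaves site out

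*Protocol article*

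**What the plan says.** All references are to the protocol article.

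- **Trial design {8}:** "Two hundred patients scheduled for THA and 200 patients scheduled for TKA will be independently randomly assigned to the IG or CG".
- **Study setting {9}:** "The study will be conducted in eight clinical sites in Germany".
- **Recruitment {15}:** "Each study site recruits both patients with knee or hip problems".
- **Sequence generation {16a}:** "A 1:1 randomization has been conducted, assigning patients to either CG or IG for THA or TKA, respectively". For this, "two randomization lists have been created using Excel random number generator, creating separate lists for THA and TKA". The section then describes blocks of 50, in which "each of the eight study sites is allocated to a fixed slot of 50 patients on the randomization list". The reason given is administrative: to stop two sites claiming the same entry in a shared online file. A site that needs more than 50 places can be given new ones at the end. The section closes with "Randomization will ensure an equal distribution of patients". It does not say that a block holds 25 codes for each arm.
- **Concealment mechanism {16b}:** describes one shared trial list with a field for hip or knee.
- **Implementation {16c}:** the ID of a patient who declines after allocation is removed.
- **Statistical methods {20a}:** the primary comparison, run separately for hip and knee, is a Student's t-test on the change from baseline to 3 months. It has no site term. Adjustment follows only if baseline differences are seen, and site is not named there.
- **Strengths and limitations:** "it cannot be excluded that clinic-internal processes or procedures influence the change in outcome".

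**The concern.** A permuted block guarantees equal arms only when it is full. If a site uses about half of a block of 50 for one indication, the split among the places used is left to chance. The closing assurance in Sequence generation {16a} then claims more than the scheme delivers.

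What is at stake is mainly the site mix of the two arms. The protocol itself treats the clinic as a possible influence on the change in outcome. If one arm happens to hold more patients from a clinic with better or worse recovery, part of that difference enters the estimated app effect, and the planned test does nothing to remove it.

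**Working it through.** The protocol gives no figure for imbalance, so there is none to reproduce.

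**Inputs.** 200 patients per indication (Trial design {8}); 8 sites (Study setting {9}); slot of 50 and 1:1 allocation (Sequence generation {16a}); effect 9 points, SD 15, so d = 0.6, and 61 analysed per group (Sample size {14}). **Assumption, not in the document:** each block of 50 contains exactly 25 codes per arm.

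**Expected use.** 200 / 8 = 25 patients per site and indication on average.

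**Imbalance within one site.** If f of the 50 places are used, the number in the intervention arm is hypergeometric. The difference between arms, D, has Var(D) = f(50 − f)/49.
- f = 25: 25 × 25 / 49 = 12.76, SD 3.57. In 95% of cases the difference is at most about 7 (16:9).
- A split of 16:9 or more extreme, in either direction, has probability about 0.089 at a given site. For at least one of eight sites it is 1 − 0.911^8 ≈ 0.53.

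**Imbalance per indication** (sum over eight independent sites).
- All sites use 25: SD = √(8 × 12.76) = 10.1. In 95% of cases the split is within about 110:90. Simulation gives P(difference ≥ 10) = 0.37 and P(exactly 100:100) = 0.08.
- Uneven use 45, 35, 30, 25, 20, 20, 15, 10: the sum of f(50 − f) is 4,100; 4,100/49 = 83.7; SD 9.1.
- Uneven use 50, 50, 40, 20, 15, 10, 10, 5: the sum is 2,550; 2,550/49 = 52.0; SD 7.2.
- Four full sites and four empty ones: SD 0.

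**Other reading of the slot.** Suppose the 50 places at a site serve hip and knee together. If 25 of them go to hip patients, those are 25 draws from the same 25:25 block, so the SD is again 3.6 per site and 10.1 per indication. If each site instead had 25 places on each list, balance would require every site to fill its places exactly.

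**If blocks are not 25:25.** The scheme then behaves like simple randomization: SD √25 = 5.0 per site and √200 = 14.1 per indication. The 25:25 assumption therefore favours the plan.

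Removal of the IDs of patients who decline is not modelled above.

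**Effect on precision.** At 110:90 the variance factor is 1/110 + 1/90 = 0.0202, against 0.0200 at 100:100. Power at d = 0.6 (two-sided 0.05) is 98.7% against 98.8%. With 61% of patients analysed (61 of 100 per group) it is 90.5% against 90.8%.

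**Effect of site mix.** With arms of about 100, a site that splits 16:9 makes up 16% of one arm and 9% of the other. About 0.07 of that site's deviation from the other sites then passes into the treatment difference. The document gives no size for clinic differences, so this cannot be put in score points.

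**The case against.** **The surplus of places is an inference.** A reader might conclude that there are 8 × 50 = 400 places on each list for 200 patients, and 800 in all. The text speaks of one list in the singular, Concealment mechanism {16b} describes a single shared list with a joint field, and 400 is also the total sample. Two separate lists make the per-list reading natural, but the document does not state it. This objection stands against any claim of a surplus. It does not rescue balance, since the shared reading gives the same SDs if each site recruits 25 per indication.

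**Half-filled blocks are only an average.** The overflow rule shows that some sites may exceed 50. This stands, and it is why a range is given.

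**The assurance may concern patient characteristics.** The sentence before it is about affinity for digital applications. That reading is plausible, but randomization balances characteristics only in expectation, so the wording is still too strong.

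**The consequence is small.** A reader might infer that the comparison is biased, underpowered or invalidly tested. None of this follows. Chance imbalance by site does not bias a randomized comparison, the power loss is a fraction of a percentage point, and an SD of 10 is better than the 14.1 of simple randomization, itself a legitimate method. All of this stands.

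**Small blocks are a debatable remedy.** The lists already exist, recruitment was planned to end in February 2022, and short blocks are easier to guess in an open-label trial. This stands, so small blocks are only an option here.

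**Conclusion.** The point holds in a limited form. Slots of 50 tied to sites, introduced for administrative reasons, do not ensure equal arms within sites or per indication. On the 25:25 assumption the SD of the arm difference is about 3.6 per site and 10 per 200 if each site recruits 25, and about 7 to 9 per 200 under the two uneven patterns tried. It reaches zero only in special cases such as four full and four empty sites.

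The weakness is that the plan names site as a possible influence on outcome, assigns places by site, and then neither balances site reliably nor includes it in the primary test. Adjusting for site costs so little that there is no good reason to leave it out.

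**What to change.** 1. For each indication, replace the two-sample t-test on the 3-month change with a linear model that has arm and site as factors, site being the unit by which places are assigned.
2. Report the split between arms by site, separately for hip and knee.
3. In Sequence generation {16a}, replace the assurance with a statement that randomization balances the arms in expectation. State whether the 50 places are per list or shared by hip and knee, and whether each block holds 25 codes per arm.
4. Optional, for places not yet released: permuted blocks of small, randomly varying size within site and indication, with upcoming entries hidden. At 25 patients per site, sizes of 4, 6 and 8 give an SD of about 3.3 per 200 and site differences of up to 3. Fixed blocks of 4 give an SD of 2.8 and a site difference of 1, but are easier to predict.

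**Cost.** Items 2 and 3 need only reporting and wording. Item 1 uses up to seven degrees of freedom per indication: with 61 analysed per group, 122 − 2 = 120 falls to 113. A site whose patients are all in one arm would add nothing to the comparison, so any pooling of very small sites should be fixed before data are seen by arm. Item 4 needs new list segments and makes the sequence somewhat more guessable.
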